## Abstract

**Background:**

The start of complementary feeding in infancy plays an essential role in promoting healthy eating habits. Evidence shows that it is important *what* infants are offered during this first introduction of solid foods: e.g. starting exclusively with vegetables is more successful for vegetable acceptance than starting with fruits. *How* infants are introduced to solid foods also matters: if parents are sensitive and responsive to infant cues during feeding, this may promote self-regulation of energy intake and a healthy weight. However, the effectiveness of the *what* and the *how* of complementary feeding has never been experimentally tested in the same study. In the current project the *what* and *how* (and their combination) are tested in one study to determine their relative importance for fostering vegetable acceptance and self-regulation of energy intake in infants.

**Methods:**

A four-arm randomized controlled trial (Baby’s First Bites (BFB)) was designed for 240 first-time Dutch mothers and their infants, 60 per arm. In this trial, we compare the effectiveness of (a) a vegetable-exposure intervention focusing on the *what* in complementary feeding; (b) a sensitive feeding intervention focusing on the *how* in complementary feeding, (c) a combined intervention focusing on the *what and how* in complementary feeding; (d) an attention-control group. All mothers participate in five sessions spread over the first year of eating solid foods (child age 4–16 months). Primary outcomes are vegetable consumption, vegetable liking and self-regulation of energy intake. Secondary outcomes are child eating behaviors, child anthropometrics and maternal feeding behavior. Outcomes are assessed before, during and directly after the interventions (child age 18 months), and when children are 24 and 36 months old.

**Discussion:**

The outcomes are expected to assess the impact of the interventions and provide new insights into the mechanisms underlying the development of vegetable acceptance, self-regulation and healthy eating patterns in infants and toddlers, as well as the prevention of overweight. The results may be used to improve current dietary advice given to parents of their young children on complementary feeding.

**Trial registration:**

The trial was retrospectively registered during inclusion of participants at the Netherlands National Trial Register (identifier NTR6572) and at ClinicalTrials.gov (NCT03348176).

Protocol issue date: 1 April 2018; version number 1.

## Background

In light of today’s global obesity epidemic and related diseases, promoting healthy eating habits is essential [1]. Children as young as 1–3 years of age already eat too much energy-dense food and too little fruit and vegetables [2–6]. In the Netherlands, based on surveys between 2006 and 2014, estimates for the percentage of preschoolers failing to meet daily recommendations for vegetable intake vary from 40% up to an alarming 80% [2, 3]. Moreover, a recent experimental study showed that almost 40% of 4 year-olds fail to effectively regulate their own energy intake, showing a tendency to eat even though they are not hungry [7]. Poor eating habits, such as consuming too little vegetables and eating in the absence of hunger increase the risk of developing overweight and obesity, and related diseases such as type II diabetes [8–12], cardiovascular disease [13], and certain cancers [14]. Both children’s food preferences and their ability to self-regulate their energy intake are influenced by their direct environment already in the first two years of life [15–20]. Therefore, promoting a healthy diet and healthy eating habits and behavior from infancy is essential. At this young age, parents bear primary responsibility for the diet of their children. The present article describes the study protocol and sample of a randomized controlled trial under the acronym *Baby’s First Bites (BFB),* aimed at (a) promoting vegetable intake and liking, and (b) promoting child self-regulation of energy intake, by advising parents *what* and *how* to feed their infants from the very start of complementary feeding. The primary goals of promoting vegetable acceptance and self-regulation of energy intake serve the purpose of reducing the risk of developing overweight in early childhood – our secondary outcome. Three interventions will be compared to an attention-control condition (1): a *repeated exposure* intervention motivating parents to repeatedly expose their children to the taste of a variety of vegetables during the first year of complementary feeding (2); a *parenting* intervention promoting sensitive parental feeding; and (3) a *combined* intervention promoting both repeated exposure to vegetables and sensitive feeding.

### Repeated exposure to a variety of vegetables from the start of complementary feeding

When parents start complementary feeding, they can choose from a variety of foods to introduce to their children, including (baby) cereals, grains, fruits or vegetables [21, 22]. Already in the 1970s it was theorized that to improve the acceptance of vegetables, these should be introduced before fruits or other sweet tastes during complementary feeding because infants’ inherent preference for sweet tastes will interfere with vegetable acceptance [23]. The effects of starting complementary feeding exclusively with vegetables on promoting vegetable acceptance has, however, not been studied often [24]. Two other methods of increasing vegetable intake and liking *have* been studied extensively. First, repeated exposure to the taste of vegetables has been shown effective in increasing its intake and liking in infants and preschoolers [24–32], especially for bitter tastes [33]. Second, being exposed to a variety of vegetables increases vegetable acceptance in infants [23, 29, 34, 35]. However, whether it is indeed most effective to start with vegetables *only* was not tested until the trial by Barends et al. in 2013 [22]. This study showed that infants exposed to a variety of vegetables during the first three weeks of complementary feeding – including a target vegetable to which they were repeatedly exposed – nearly doubled their intake of the target vegetable, whereas children who only received fruits showed increased intake of fruits but not of vegetables [26]. Shortly after this trial, another intervention study found similar results: encouraging parents from the United Kingdom to start complementary feeding with a variety of vegetables significantly increased vegetable intake compared to a control group in which parents were allowed to start complementary feeding with whatever food they wanted [36].

Thus, there is preliminary evidence that starting complementary feeding by repeatedly exposing infants to a variety of vegetables is an effective way to increase vegetable intake and liking in the first year of a child’s life. However, the beneficial effects on vegetable acceptance do not seem to last when children grow older [27, 30, 37]. This is in line with the finding that children are open to trying a variety of different tastes in their first year of life, but tend to become more selective about their diet when they become older (especially in the ‘food neophobic phase’) [24, 38, 39]. Indeed, in the Barends et al. trial, starting complementary feeding with vegetables did *not* predict vegetable intake at age two, whereas how selective children were about what they wanted to eat did [27]. Continuing the active promotion of eating vegetables in the first and second year of the child’s life after exposing them to a variety of vegetables at the start of complementary feeding may counteract the negative effects of the food neophobic phase and effectively boost vegetable intake throughout childhood. However, most intervention studies have been conducted with infants in the early phases of complementary feeding or preschoolers older than 2 years; few studies focus on promoting vegetable acceptance in the difficult period between 12 and 24 months when children go through the major transition of eating the same meals as their family and enter the food neophobic phase [40, 41]. Therefore, we studied the effectiveness of a more prolonged vegetable-exposure intervention throughout the whole first year of complementary feeding, well into the more ‘difficult’ second year of the child’s life to promote vegetable intake in toddlers.

### Sensitive feeding

Apart from *what* parents should offer their children during complementary feeding, *how* they offer this food may also strongly influence a child’s acceptance of the offered food, as well as their ability to self-regulate their energy intake. Experimental studies show that pressuring a child to eat decreases children’s ability to self-regulate their energy intake and thereby to consume appropriate amounts of calories [42]. Similarly, pressuring a child to eat vegetables has a counterproductive effect and will make a child eat and like these vegetables less [43]. Even giving subtle prompts to eat, like moving food towards a child, may have a counterproductive effect [44]. However, if children start to decrease their vegetable intake when they enter the second year of life, parents are likely to use some sort of pressure to make their child eat. Indeed, an Australian study showed that more than half of the parents of 1–3 year-olds sometimes insist on their child eating a food, and 35% reported to pressure their child often or all the time [45]. As such, it is not surprising that many parents struggle with the question how to feed their infants effectively. Indeed, 25 to 40% report feeding problems with their infants and toddlers, including picky eating and strong food preferences [46, 47].

In contrast to pressuring children to eat, *responsive feeding* is often suggested to be the optimal way to feed infants and toddlers [48–51]. Responsive feeding is generally defined as a style of feeding in which parents correctly perceive the hunger and satiety signals of the child, and respond promptly and appropriately [50, 52]. This feeding style is suggested to promote and reinforce young children’s ability to self-regulate their energy intake, because the parent who feeds responsively will not override a child’s satiety cues [50]. Indeed, promoting responsive feeding was shown to be associated with a reduced risk of overweight and of rapid weight gain during the first years of life [50, 53, 54]. However, although attending to hunger and satiety signals may promote child self-regulation of energy intake, it may not be sufficient to promote healthy food preferences including vegetable acceptance during the first years of the child’s life. As children from the age of 1.5 years become more and more autonomous and selective about their food preferences, parents have to manage that their child eats appropriate quantities, but also the specific (healthy) foods that are served. To promote healthy food preferences, parents will need to stimulate their child to eat vegetables in a non-pressuring way that is sensitive to the child’s autonomy-related needs and behaviors. This requires more than just responsiveness to hunger and satiety cues, but also sensitive discipline strategies to challenging child behavior (e.g. when a child throws their food on the ground) and sensitive responses to distracted behavior (e.g. when a child is more interested in what is happening around them than in its plate of food). Sensitive discipline strategies that parents may use entail positive encouragement (e.g. explicitly complimenting the child for positive behavior), appropriate pacing to allow the child sufficient time to adapt to the situation, granting the child appropriate amounts of autonomy (e.g. allowing the child to eat autonomously when the child is able to and shows it wants to) and showing understanding for the child’s point of view [55]. Using these sensitive discipline strategies has been shown to promote infant’s committed compliance, i.e. internally motivated and self-regulated adherence to parental rules [56]. In the current study we introduce the concept *sensitive* feeding to capture this broader set of sensitive parenting skills relevant to promoting children’s committed compliance to parental attempts to feed them healthy foods. Sensitive feeding thus includes the traditional concept of responsive feeding [50, 52], but with the addition of sensitive discipline as well as autonomy support, also in response to non-food related child behaviors during feeding. We hypothesize that parents showing sensitive feeding will be more successful in increasing their children’s vegetable acceptance.

In recent years a number of randomized controlled trials to promote responsive feeding have been performed, some of which incorporated the discipline component described above [57–62] whereas others merely focused on teaching parents how to effectively respond to the hunger and satiety cues of their child [53, 54]. However, none of these interventions focused on promoting responsive or sensitive feeding alone. Instead, they incorporated a much broader range of topics such as dietary advice, advice on general feeding practices, guidelines for physical activity, or even more broad advice on how to manage the sleeping and crying behavior of the child. As such, it is impossible to isolate the specific effect of responsive feeding on the diet and eating behavior of the child, and whether this is in fact an element that should be targeted to promote healthy eating patterns. Moreover, all previous trials evaluated changes in parenting behavior via self-report questionnaires, whereas expert observations of parent-child interaction is considered the gold standard to measure parenting behavior [63]. An important disadvantage of self-reports of parenting behavior specifically is that it is questionable whether these data represent the actual parenting behavior parents show, or rather attitudes about what they think they are or should be doing. Indeed, the correlation between self-reported and observed parenting behavior is often low, both in the field of parental feeding [64–66] and in other fields [67]. Therefore, we will test the effectiveness of an intervention focusing solely on the enhancement of sensitive feeding, by evaluating its outcomes using repeated observations of family meals at home in addition to self-reports.

### Repeated exposure and sensitive feeding

Whether a combination of repeatedly exposing infants to vegetables and encouraging sensitive feeding may lead to a better vegetable intake and liking than each of the interventions alone, has never been tested before. However, there is evidence that presentation of beneficial food choices (succeeding at the *what*) in a non-responsive manner (failing at the *how*), and the presentation of unhealthy food choices (failing at the *what*) in a responsive manner (succeeding at the *how*) may lead to overweight and eating problems in children [43, 68]. For instance, an experimental study by Galloway and colleagues showed that pressuring a child to eat, even if this pressure is mild in nature, decreases the beneficial effects of repeated exposure to the taste of vegetables [43]. This suggests that an intervention aimed at both elements may be particularly powerful.

### Aims and hypotheses

In summary, the *Baby’s First Bites (BFB)* study aims to test whether promoting the *what* and**/**or promoting the *how* of complementary feeding will result in increased vegetable consumption and liking and a better self-regulation of energy intake in infants and toddlers up until the age of 36 months. To this end, we will perform a superiority randomized controlled trial with parallel groups, comparing a) an intervention focusing on vegetable exposure (=what), b) an intervention focusing on sensitive feeding (=how), c) an intervention focusing on vegetable exposure and sensitive feeding (=what and how), and d) a control condition. The interventions will begin when the infant starts receiving complementary food (child age 4–6 months, as recommended by the Dutch Nutrition Center) and continue until the child is 16 months old. We hypothesize that a) all interventions are more effective in improving vegetable consumption and vegetable liking than the control condition without guidance on complementary feeding; b) the sensitive feeding and combined intervention will be more effective in supporting child self-regulation of energy intake than the vegetable exposure or control conditions; and c) the combined intervention is more effective than the other two interventions alone in promoting vegetable intake and vegetable liking. As the inclusion phase of the *BFB* study has already successfully been completed, the present article describes the characteristics of the sample of included participants as well as the design of this ongoing study.

## Methods/design

### Study design

The *BFB* study is a collaboration between Leiden University, Wageningen University and Research, Danone Nutricia Research and Nutricia Early Life Nutrition. The study is a multicenter trial that is currently being performed at Leiden University and Wageningen University and Research, using a superiority randomized controlled design. The protocol has been approved by the Ethical Review Board of Education and Child Studies, Leiden University (protocol number ECPW-2015/116) and the Medical Ethical Review Board of Wageningen University and Research (METC-WU protocol number NL54422.081.15). The inclusion phase started in May 2016 and ended successfully in November 2017. Mothers and their 4–6 month-old infant were randomly allocated to receive either repeated exposure to a variety of vegetables (RVE), the parenting intervention Video-feedback Intervention to promote Positive Parenting-Feeding Infants (VIPP-FI), RVE and VIPP-FI combined, or an attention-control intervention (see Fig.1 and Table 1). Families receiving the RVE intervention were further randomly allocated to one of two types of vegetables the infant is repeatedly exposed to (see *Interventions* below): green beans or cauliflower. Two target vegetables were chosen as the current feeding schedule is based on the 19-day feeding schedule as described by Barends and colleagues [26, 27]. Green beans and cauliflower are commonly consumed in the Netherlands. Randomization into these conditions was done using the online program TenALEA, which assured that the exact same randomization procedure was used at both study sites [69]. To make the groups allocated to the different conditions as comparable as possible concerning relevant potential confounders, randomization was stratified by age of the child at the start of complementary feeding (4, 5 or 6 months), gender of the child and study location, using minimization procedures. The online randomization program TenALEA has been used previously in other clinical trials [70, 71]). Participants were allocated to a condition by one of the PhD-students or research assistants at each study location.

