	Enrolment	Intervention-period						Post-test	Follow-up	
Child age (in months)	2–4	4–7		8	12	13	16	18	24	36
Time point		*t* _*0*_	*t* _*1*_		*t* _*12*_			*t* _*18*_	*t* _*24*_	*t* _*36*_
Enrolment & allocation										
1. Invitation e-mail	x									
2. Information and informed consent	x									
3. Screening	x									
4. Allocation	x									
5. Rice-flour porridge	x									
Interventions										
RVE										
Feeding schedule		days 1–19								
Phone-call		Twice in period days 3–17		x		x	x			
Provision of vegetable purees		X		x	x					
VIPP-FI										
Feeding schedule		days 1–19								
Home-visit		Twice in period days 3–17		x		x	x			
Provision of fruit and carrot purees		X		x	x					
Combined RVE + VIPP-FI										
Feeding schedule		days 1–19								
Phone-call + home-visit		Twice in period days 3–17		x		x	x			
Provision of vegetable purees		X		x	x					
Attention-control										
Feeding schedule		days 1–19								
Phone-call		Twice in period days 3–17		x		x	x			
Provision of fruit and carrot purees		X		x	x					
Assessment of study outcomes^a^		Days 1 + 2	Days 18 + 19		x			x	x	x

*Note.*
^a^Primary outcomes: vegetable intake and liking, child self-regulation of energy intake. Secondary outcomes: child anthropometrics, child eating behavior and maternal feeding behavior. RVE = repeated exposure to vegetables. VIPP-FI=Video-feedback Intervention to promote Positive Parenting-Feeding Infants

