### Analyses

The intention-to-treat principle will be applied to all analyses. Whether the interventions differentially affect primary and secondary outcomes over time will be analyzed using linear mixed models analyses, a technique that makes use of every data point for every participant, irrespective of their missing data. The three intervention groups will be compared to the control group, and the combined group will be compared to the repeated exposure and the VIPP-FI group. A significance level of α = .05 will be used. The analyses will be corrected for relevant covariates such as family socioeconomic status, maternal consumption of vegetables, parental body mass index (BMI), child temperament, etc.

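### The three minimization factors (study location, child gender, age at start of feeding) are not named as model terms, and leaving them out would make tests somewhat conservative if they are prognostic

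*Protocol article*

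**What the plan says.** Under Study design, the protocol article states that "randomization was stratified by age of the child at the start of complementary feeding (4, 5 or 6 months), gender of the child"; the third factor was study location. The balancing was done "using minimization procedures". The reason given is to make the arms comparable on likely confounders.

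Under Analyses, effects over time on primary and secondary outcomes "will be analyzed using linear mixed models analyses". The correction is for "relevant covariates such as family socioeconomic status, maternal consumption of vegetables, parental body mass index (BMI), child temperament, etc". None of the three minimization factors appears there. The longer list of potential covariates under Other measures does not name them either.

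On testing, the article says only: "A significance level of α = .05 will be used". It does not say whether tests are one- or two-sided.

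On timing, Table 2 places the block headed "Enrolment & allocation" in the column for child age 2–4 months. Eligibility (Recruitment and participants) requires that the family plans to start feeding at 4–6 months. The text after Table 1 says that parents started when they judged the child ready. Study design, however, describes the infants as 4–6 months old when it reports the allocation.

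**The concern.** Minimization makes the arms more alike on the chosen factors than simple randomization would. Where such a factor predicts the outcome, the true sampling variation of the difference between arms is therefore smaller. A model without the factor leaves its variance in the residual, so the reported standard error is too large and the test rejects too rarely.

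The design singled out three variables for balancing. The two places that discuss covariates name others and not these. If the analysis follows only the named list, precision secured by the design is not used. There is also an ambiguity about age: the stratum entered at allocation and the actual starting age may differ, and the plan does not say which would be used.

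**Working it through.** **Inputs.** From Calculation of sample size: effect size 0.50 (taken as a standardized mean difference, SD 1), power 0.80, alpha 0.05, 51 per group, 60 per group after attrition. The share of outcome variance explained by the three factors, R², is not in the documents, so it is varied from 0% to 10%.

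**The plan's own figure.** With the normal approximation, n per group = 2(z_α + z_β)²/0.5².
- One-sided: 2(1.645 + 0.842)²/0.25 = 49.5, so 50. The exact t calculation gives 51 (power 80.6%), which matches the article.
- Two-sided: 2(1.960 + 0.842)²/0.25 = 62.8, so 63. The exact t calculation gives 64. With 51 per group, two-sided power is about 71%.
- Attrition: 51/0.85 = 60, so the implied attrition is 15%.

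Sidedness is not stated, so both versions are carried forward.

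**Effect of omitting the factors, for a comparison at one time point.** Let k = √(1 − R²) and λ = 0.5·√(51/2) = 2.525.
- Standard error inflation without the factors: 1/k − 1.
- Two-sided type I error without the factors: 2·(1 − Φ(1.960/k)).
- Power without the factors: Φ((λ − z)/k).
- Power with the factors: Φ(λ/k − z).

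Example, R² = 10%, two-sided: k = 0.9487. Without: Φ((2.525 − 1.960)/0.9487) = 72.4%. With: Φ(2.525/0.9487 − 1.960) = 75.9%. The difference before rounding is 3.4 points.

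| Assumed R² | SE inflation | Two-sided type I error, factors omitted | Two-sided power, omitted → included | One-sided power, omitted → included |
|---|---|---|---|---|
| 0% | 0% | 5.0% | 71.4 → 71.4% | 81.1 → 81.1% |
| 2% | 1.0% | 4.8% | 71.6 → 72.3% | 81.3 → 81.7% |
| 5% | 2.6% | 4.4% | 71.9 → 73.6% | 81.7 → 82.8% |
| 10% | 5.4% | 3.9% | 72.4 → 75.9% | 82.3 → 84.5% |

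Power forgone, from unrounded values: 0, 0.7, 1.7 and 3.4 points two-sided; 0, 0.4, 1.1 and 2.2 points one-sided.

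**Check by simulation.** Four-arm minimization, 204 children in total, assumed stratum shares, 1,500 runs, two-sided. The Monte Carlo standard error is about 0.6 points for type I error, √(0.05·0.95/1500), and about 1.1 points for power.
- R² = 10%: type I error 4.1% without and 5.1% with the factors; power 73.3% and 76.3%.
- R² = 5%: type I error 4.9% and 5.5%; power 71.2% and 72.4%.

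Within that error, these agree with the formulas.

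**Which outcomes it reaches.** Intake from t12 comes from 24-hour recalls, whereas at t0 it is weighed puree. Eating in the absence of hunger (EAH) is first measured at t18. Neither has a comparable baseline, so the table applies to them. For a group-by-time contrast with a baseline in a random-intercept model, the random intercept takes up most of the between-child variance due to time-constant factors. Adding their main effects then changes the contrast's standard error little.

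**Sparse stratum.** Actual starting age has mean 4.68 and SD 0.42 months, so 6.0 months lies (6.0 − 4.68)/0.42 = 3.1 SDs above the mean. Few infants can have started at 6 months or later, although the strata as entered are not reported.

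**The case against.** The strongest objection is that nothing shows the factors will be left out. The covariate list is introduced as examples and ends open, the article condenses a fuller protocol, and a final covariate list is often left to the statistical analysis plan. This stands against any claim that the standard errors will ignore the balance or that power is lost. A reader might infer that from the named covariates, but the text neither includes nor excludes the three factors. What remains is narrower: the article chose to name covariates, and it did not name the three that the allocation itself used.

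Second, the size is assumed and may be near zero. Starting ages are concentrated, assessments from t12 are at set child ages, and the relevant R² is what the factors add beyond the other covariates. This stands, and is why the range starts at 0%.

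Third, a reader might infer that an already underpowered trial becomes weaker still. The documents do not support this. The figure of about 71% assumes a two-sided test, which the article does not state; 51 per group reproduces as a one-sided calculation. Nor does omission push power below its value at R² = 0: two-sided, it moves from 71.4% to 72.4% at R² = 10%. Only a possible gain is given up.

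Fourth, a reader might take it as established that only the planned starting age was known at allocation. That is an inference from Table 2 and the eligibility wording, and it conflicts with the description of 4–6-month-old infants under Study design. No text says which age was entered in the randomization program.

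**Conclusion.** The point holds in a limited form. The plan minimizes on three factors and does not commit to any of them as a model term, though its open list leaves room for them. If they are omitted and are prognostic, the error is in the conservative direction. For outcomes without a comparable baseline, R² up to 5% costs less than 2 points of power at 51 per group, and 10% costs 3.4 points two-sided or 2.2 one-sided. If the factors are not prognostic, nothing is lost. For group-by-time contrasts in a random-intercept model the effect is small, so the tabulated figures should not be applied to every model. False-positive risk is not raised and the planned sample size is not invalidated.

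These sizes rest on the assumed R², on 51 analysed per group, on a standardized effect of 0.50, and on a comparison at one time point.

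**What to change.** In the Analyses section, name study location, child gender and the age stratum as fixed effects in the primary and secondary models, ahead of any optional covariate. State that the age stratum is the value entered in the randomization program, not the actual starting age. On Table 2's timing, the actual age is known only after allocation. The allocation age in Table 2 and the description under Study design should be reconciled at the same time.

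The cost is a sentence and up to four degrees of freedom (location 1, gender 1, age 2). The three factors were needed for allocation, so no new data should be required. The 6-month stratum is likely to be sparse and may need merging with the 5-month stratum; that rule should be written down before the data are analysed.
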